### Data management

The NICTU will provide training to site staff on trial processes and procedures including CRF completion and data collection. Source data verification (SDV) will be completed by the NICTU and will check the accuracy of entries on the electronic CRF against the source documents and adherence to the protocol. The extent of SDV to be completed is detailed in the Monitoring Plan. Quality control is implemented by the NICTU in the form of SOPs, which encompass aspects of the clinical data management process, and ensure standardisation and adherence to GCP guidelines and regulatory requirements. Data validation will be implemented, and discrepancy reports will be generated following data entry to identify discrepancies such as out of range, inconsistencies or protocol deviations based on data validation checks programmed in the clinical trial database. Following the entry of patient data into the study database, the data will be processed as per NICTU SOPs and the study specific Data Management Plan. Data queries will be generated electronically for site staff to clarify data or provide missing information. The designated site staff will be required to respond to these queries. All queries will be responded to or resolved within the study database and amended in the study database.

### Statistical methods

The primary analysis will be conducted on outcome data from all randomised patients according to the group to which they were allocated (i.e. intention-to-treat), regardless of the subsequent treatment they received. Trial results will be reported in accordance with Consolidated Standards of Reporting Trials guidance (CONSORT)
^
37
^. It is possible that some participants may not receive the full treatment dose, therefore a secondary per protocol analysis will be undertaken on the population who receive the complete treatment dose. Baseline characteristics, follow-up measurements and safety data, will be described using suitable measures of central tendencies; means and medians with the associated standard deviations, 95% confidence intervals, and interquartile ranges for continuous data; and frequencies and proportions for categorical data (including binary data). 

Primary outcomes for the randomised groups will be compared using a Cox proportional hazards model including site and adjusting for age and illness severity (APACHE II). For this analysis, no interaction between interventions will be assumed. Comparison for other continuous outcomes will use analysis of covariance to adjust for baseline characteristics and covariates. Comparison for binary outcomes will use generalised linear models (GLMs) as appropriate to estimate risk ratio and risk differences. 95% CI and p-value will be presented alongside the estimates. Analyses will be two-sided and tested at an
*a priori* significance level of p=0.05. The factorial design permits separate testing of the effects of carbocisteine and hypertonic saline on outcomes. Although there is no biologic rationale for, or expectation that, either mucoactive will have an effect on death, a sensitivity analysis for competing risk of death will be included. Sensitivity analyses will also be included to investigate the impact of any potential interaction between the interventions on the primary analysis, to investigate the impact of contamination between the interventions, and to investigate the impact of compliance on the primary analysis. 

An independent NICTU statistician will conduct an interim analysis for the primary outcome when 60-day follow-up is available for 978 patients (half the estimated sample size), to ascertain whether assumptions made in the sample size calculations are correct. In accordance with the Haybittle-Peto stopping rule, the DMEC will be asked to make a recommendation about the future of the trial, considering the likely impact of the interim result on future practice and a p-value of less than 0.001 as "significant".

## Methods for additional analyses

Exploratory analyses for the primary outcome will be reported using interaction tests (treatment group by subgroup) and 99% confidence intervals for the following subgroups:

i)   Baseline APACHE II score

ii)   Baseline PaO
_2_/FiO
_2_ (PF) ratio

iii)   Pre-existing chronic respiratory condition prior to randomisation

iv)   Neurological diagnosis prior to randomisation

v)   Admission diagnostic categories; pulmonary vs. non-pulmonary

vi)   Receiving antibiotics for pulmonary infection at randomisation

The following Intercurrent Events have been identified which would prevent measurement of the primary outcome or change the interpretation of the measured primary outcome:

1.   Death prior to the timepoint at which randomised treatment is due to start

2.   (a) Hypertonic saline allocated in randomisation but not started

      (b) Carbocisteine allocated in randomisation but not started

3.   Death before successful unassisted breathing. 

4.   Transfer to another ICU before successful unassisted breathing. 

5.   Use of non-trial mucoactives 

6.   Patient withdrawal from intervention

Events 1, 2(a) and 2(b) are expected to be rare and no specific actions will be taken: analysis of these events will be by intention to treat, except for event 1 which will be handled in the same way as event 3. Event 3 will be treated as a competing risk for the primary outcome and will therefore be analysed using a hypothetical strategy. Event 5 will be dealt with using an intention to treat approach. Event 6 will also be handled using a hypothetical strategy, in which the time to unassisted breathing will be censored at the point of withdrawal and the withdrawals will be assumed to lead to missing at random data on the primary outcome. Complete follow-up should still be possible for most participants in whom event 4 occurs; if not, the hypothetical strategy used for event 6 will also be implemented.

Further details and a full description of all analyses are provided in the Statistical Analysis Plan available at
https://nictu.hscni.net/service/march-trial/march-trial-documents/).

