### Outcomes

**
*Primary outcome*
**

The primary outcome is the duration of mechanical ventilation (in hours). This is defined (measured) as time from randomisation until first successful unassisted breathing (defined as maintaining unassisted breathing at 48 hours) or death. This outcome is one of the ‘COVenT’ core outcomes for trials of interventions intended to modify the duration of mechanical ventilation
^
19
^. To clarify:

i)   Unassisted breathing is defined as no inspiratory support or extracorporeal lung support

ii)   Success is defined as maintaining unassisted breathing at 48 hours

iii)   Duration includes time receiving extracorporeal lung support, invasive mechanical ventilation and non-invasive ventilation delivering volume or pressure support ventilation

iv)   Duration excludes time receiving high-flow oxygen therapy and continuous positive airway pressure

v)   Patients with a tracheostomy in situ may still achieve successful unassisted breathing

vi)   Follow-up to 60 days from randomisation

**
*Secondary outcomes*
**

Secondary clinical and safety outcomes, timing of their assessment, and measurement tools, are summarised in
Table 1. The secondary outcomes of extubation, re-intubation, duration of ICU and hospital stay, all-cause mortality, and health-related quality of life represent the remaining outcomes in the COVenT core outcome set
^
19
^. Data contributing to the economic evaluations also represent those items recently recommended as a priority for this purpose
^
20
^. Clinical and safety outcomes will be measured at baseline and daily up to and including Day 28 (or the primary outcome is reached), or ICU discharge, or death, whichever comes first. Where unassisted breathing begins on Day 27 or Day 28, clinical and safety outcomes will be recorded up to Day 29 or Day 30, respectively. Participants will be followed-up to 60 days post-randomisation for the outcomes of duration of mechanical ventilation, extubation and reintubation. Health-related quality of life and all-cause mortality will be measured at 60 days, and at 6 months.

**Table 1. T1:** Detail of secondary outcomes.

Outcome	Measurement tool, definition, method
In hospital	
Extubation	Time from randomisation to first successful extubation (success defined as remaining free from endotracheal or tracheostomy tubes at 48 hours); Censored at 60 days

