### Sample size

The total sample size is 1956 (489 in each of the four randomised groups). The sample size has been calculated using a median duration of mechanical ventilation of 7 days
^
4,
21
^ with a minimal clinically important difference of 1 day
^
22
^, resulting in a median duration of 6 days in the three intervention groups. This minimum clinically important value is also based on discussion with patient and family member advisors, who emphasised the importance of reducing time spent on the ventilator as a priority outcome
^
23
^. This median duration of mechanical ventilation and 1 day reduction treatment effect result in a hazard ratio of 0.86. Based on a log-rank test and at 90% power and a significance level of 0.05, this requires a sample size of 1856 (464 in each of the four randomised groups). Previous critical care trials have demonstrated low levels of loss to follow-up, at less than 5%
^
24–
28
^, and the nature of the proposed trial where all primary outcome data will be acquired whilst patients are in the ICU and identifiable to the research team, should minimise loss to follow up. Allowing loss to follow at the 5% level, requires a sample size of 1956 (489 in each of the four randomised groups).

As there is no clinical or biological rationale for, or expectation of, any interaction between the two mucoactives, the sample size has not been inflated for this purpose. This is in keeping with systematic review findings highlighting appropriate restriction of the factorial design to scenarios where treatments do not have the potential for substantive interaction
^
29
^.

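### The primary outcome counts death as an end of ventilation in one section and as a competing event under a hypothetical strategy in another, and the stated 90% power fits only the first

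*Protocol article*

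**What the plan says.** All references are to the protocol article.

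- **Outcomes, primary outcome.** Duration of ventilation is "time from randomisation until first successful unassisted breathing (defined as maintaining unassisted breathing at 48 hours) or death", followed to 60 days. Death is part of the endpoint.
- **Methods for additional analyses, intercurrent events.** Death before successful unassisted breathing is event 3, and "Event 3 will be treated as a competing risk for the primary outcome and will therefore be analysed using a hypothetical strategy". Event 1, death before treatment is due to start, follows the same rule. The strategy is spelled out only for event 6, withdrawal from the intervention: "the time to unassisted breathing will be censored at the point of withdrawal", with data assumed missing at random.
- **Statistical methods.** "Primary outcomes for the randomised groups will be compared using a Cox proportional hazards model including site and adjusting for age and illness severity". Whether a death is an event or a censoring in that model is not stated. The section adds that "a sensitivity analysis for competing risk of death will be included", having noted that no effect on death is expected.
- **Sample size.** A fall in median duration from 7 to 6 days, hazard ratio 0.86, log-rank test, 90% power and significance level 0.05 give 1856 patients. Five per cent loss to follow-up raises this to 1956. No mortality figure is given, and there is no allowance for deaths that are not events.

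**The concern.** Death cannot be both a component of the endpoint and an intercurrent event that prevents the endpoint from being measured. The two rules give different estimands and different event counts.

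The link from competing risk to hypothetical strategy does not settle the matter. A competing-risk analysis accepts that a patient who has died can no longer be liberated, and it may be cause-specific or based on the subdistribution. A hypothetical strategy asks what would have happened had the patient not died. Censoring under missing at random, the device described for event 6, would treat patients who die on the ventilator as if they had the same prospects as those still ventilated.

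At stake are the meaning of the primary hazard ratio and the power behind it. If death is an event, it counts in the same direction as liberation. If deaths are censored, the trial has fewer events than it was sized for.

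**Working it through.** **Inputs from the article:** hazard ratio 0.86 (6/7 = 0.857), 90% power, significance level 0.05 two-sided, 1:1 for each factorial comparison, 1856 patients before loss and 1956 after, 60 days of follow-up. **Assumed:** the share *m* who die before liberation, 10% to 40%, because the article gives none. Hazards are taken as constant.

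**1. Reproducing the plan.** With (1.960 + 1.282)² = 10.51:
- Freedman: 10.51 × (1.86/0.14)² = 1855 events.
- Schoenfeld: 4 × 10.51 / (ln 0.86)² = 1848 events.
- Rounding 1855 up to four equal groups gives 464 × 4 = 1856. Then 464/0.95 = 488.4, so 489 × 4 = 1956.

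The stated number of patients is the required number of events, so every retained patient must have one. With exponential times and a 7-day median, 1 − 2^(−60/7) = 99.7% of durations end by day 60. The calculation therefore closes if death is an event or if nobody dies before liberation.

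**2. Deaths censored.** Events = 1856 × (1 − *m*). Power = Φ(√events / 2 × |ln 0.86| − 1.96).

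**3. Deaths as events, hazard ratio 0.86 on liberation only, equal death hazards.** Composite hazard ratio = 1 / [*m* + (1 − *m*)/0.86], with 1856 events. At *m* = 30%: 1 / (0.30 + 0.70 × 1.163) = 0.898. Power = Φ(√1856 / 2 × |ln 0.898| − 1.96) = 64%.

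| *m* | Events if deaths censored | Power, censored | Patients needed for 90%, before loss | Composite HR, liberation-only effect | Power, composite |
|---|---|---|---|---|---|
| 10% | 1670 | 87% | 2062 | 0.872 | 84% |
| 20% | 1485 | 83% | 2319 | 0.885 | 75% |
| 30% | 1299 | 78% | 2650 | 0.898 | 64% |
| 40% | 1114 | 71% | 3092 | 0.911 | 52% |

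Simulated log-rank tests (3000 runs per scenario, 1856 patients) gave 82%, 78% and 72% with deaths censored, and 75%, 65% and 50% for the composite, at 20%, 30% and 40%. With no deaths the simulation gave 88%, against 90% by formula.

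If all 1956 patients are analysed with no other loss and deaths are censored, power is 89%, 85%, 80% and 73% at 10%, 20%, 30% and 40%. It stays at 90% only if deaths are below about 5% (about 9% at the unrounded 6/7).

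**4. Deaths as events, hazard ratio 0.86 on the composite itself.** There are 1856 events and power is 90%, as stated. With no effect on death and *m* = 30%, this needs a rise in the liberation hazard of (1.163 − 0.30)/0.70 = 1.23, that is 23% rather than 16%.

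**The case against.** The text can be harmonised in more than one way. The definition of the primary outcome may say only when the clock stops, with deaths then censored in the Cox model. Or the intercurrent-event rule, which sits under additional analyses, may describe the competing-risk sensitivity analysis. The sensitivity analysis itself is compatible with either primary coding. These points stand, and they leave two candidate codings rather than three incompatible ones. They do not say which is meant. The statistical analysis plan, not shown here, may fix the coding, but it cannot remove a conflict inside the article.

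A reader might infer more, and the article does not support it:

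- **That either the answer or the power fails under every reading.** Sample size works from the median duration of ventilation, and Outcomes ends that duration at breathing or death. On that reading 90% is reproduced.
- **That harm would pass for benefit.** With 30% deaths, no effect on liberation and an assumed death hazard ratio of 1.3, the composite hazard ratio is 0.70 + 0.30 × 1.3 = 1.09. A significantly shorter duration then appears in about 46% of simulated trials, against about 2% with deaths censored. At 10% deaths the composite figure is about 9%. At the interim, with about 978 events, the chance of crossing p<0.001 is about 2.6%. All this needs an effect on death that the article does not expect. Mortality is also a separate outcome, and the monitoring committee's rule is not automatic.
- **That the sponsor could choose a reading after seeing results.** Without the statistical analysis plan this cannot be judged.

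**Conclusion.** The concern holds as a conflict to be reconciled. Outcomes and the intercurrent-event list give different rules for death in the primary outcome, and Statistical methods does not decide between them. The 90% is correct only if deaths are events and the 0.86 refers to time to breathing or death. Otherwise power is about 87% to 71% (deaths censored) or 84% to 52% (deaths as events, effect on liberation only). Those ranges rest on an assumed 10% to 40% dying before liberation and on constant hazards, so they show sensitivity and are not forecasts. Which estimand should be primary is partly a matter of choice. That there should be only one is not.

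**What to change.** Before the final analysis, state one coding of death for the primary Cox model and use it in Outcomes, Sample size, Statistical methods and the intercurrent-event list. Remove the hypothetical-strategy wording for event 3, and with it for event 1.

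- **If death stays an event:** state that the 90% assumes this and that 0.86 refers to the composite of breathing or death.
- **If death is a competing event:** restate power at the expected number of liberations.

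Under either coding, report three results beside the primary one: the cause-specific hazard ratio for liberation, the day-60 cumulative incidence of liberation with patients who die counted as not liberated, and the hazard ratio for death. Give the monitoring committee the death result alongside the p<0.001 rule.

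The cost is amended wording, a little more analysis on data already collected, and possibly a lower stated power. Timing matters: 1820 of 1956 patients were enrolled by 31 January 2025, and the trial is open label with an unblinded trial statistician. The change should therefore be dated and made without reference to results by group.

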### Withdrawal of consent

The ProfLR, the PerLR, or the participant may withdraw consent from the study at any time without prejudice. If consent is withdrawn this will be documented in the patient’s notes and in the CRF. The elements of the trial to be withdrawn (from the following possibilities) will be documented:

•   Mucoactive administration if ongoing

•   On-going data collection during hospital admission

•   On-going data collection following hospital discharge

•   Confirmation of vital status

If the patient or patient representative declines on-going participation, anonymised data recorded, and samples taken up to the point of withdrawal, will be included in the trial analysis unless the patient or patient representative requests otherwise. 

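### Event 6 censors the primary outcome at withdrawal from the intervention, against the stated intention-to-treat analysis, even where the outcome can still be observed

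*Protocol article*

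**What the plan says.** Two rules in the protocol article apply to the same patients and the same outcome.

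- **Statistical methods.** The primary analysis covers everyone randomised, and patients are analysed "according to the group to which they were allocated (i.e. intention-to-treat), regardless of the subsequent treatment they received".
- **Methods for additional analyses.** The article lists intercurrent events that "would prevent measurement of the primary outcome or change the interpretation of the measured primary outcome". Event 6 is "Patient withdrawal from intervention". It is given a hypothetical strategy under which "the time to unassisted breathing will be censored at the point of withdrawal". The assumption stated for this censoring is that "the withdrawals will be assumed to lead to missing at random data on the primary outcome".

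Three other places bear on how these fit together.

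- **Withdrawal of consent.** The elements a patient or representative may withdraw are recorded separately. One is "Mucoactive administration if ongoing". In-hospital data collection is another.
- **Sample size.** Primary outcome data are expected to be captured while patients are in the ICU and known to the research team.
- **The other intercurrent events.** A patient who never starts the allocated drug (2a, 2b) stays under intention-to-treat. For non-trial mucoactives, "Event 5 will be dealt with using an intention to treat approach". Transfer to another ICU (event 4) is censored only where complete follow-up proves impossible. Event 6 carries no such condition.

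**The concern.** A patient who stops only the mucoactive remains in the ICU with data collection continuing, so the time to unassisted breathing will normally be known. Followed as written, event 6 discards that time and treats it as missing. The intention-to-treat statement would keep it. Both rules cannot govern the same patient in the primary analysis.

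The censoring also depends on allocation, because the usual-care group has no trial drug to withdraw from. If those who withdraw differ in prognosis from those who stay, censoring them unequally across the comparison biases the primary hazard ratio. Each case also costs an event.

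Timing adds to this. The Trial status section reports 1820 of 1956 patients enrolled by 31 January 2025. The trial is open-label and its statistician is unblinded. If two incompatible rules stand, the choice between them could be made with allocation and outcomes known.

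**Working it through.** **1. The plan's own figure.** Inputs from Sample size and Statistical methods: hazard ratio 0.86, 90% power, two-sided 0.05. Freedman's formula gives events = (1.960 + 1.282)² × ((1 + 0.86)/(1 − 0.86))² ≈ 1855, against 1856 stated (464 × 4). Schoenfeld's formula gives 1848. Inflation: 464/0.95 = 488.4, rounded up to 489, and 489 × 4 = 1956. The sample size reproduces, so no stated number is wrong. The fault lies in the rules.

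**2. Who can be censored.** The main comparisons (Primary objective) are use against non-use of each agent. For carbocisteine:

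| Side | Groups | Can withdraw from a mucoactive |
|---|---|---|
| Use | carbocisteine; combination | both |
| Non-use | hypertonic saline; usual care | hypertonic saline only |

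If a share w of each mucoactive group withdraws, the use side loses w and the non-use side w/2. At w = 10% that is 10% against 5%. The hypertonic saline comparison is the mirror image.

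**3. Loss of events.** Three of the four groups can lose events, so events = 1856 × (1 − 0.75w). Power is Φ(|ln 0.86| × √events/2 − 1.96). The values of w are assumptions.

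| w | Events | Power |
|---|---|---|
| 0 | 1856 | 90.1% |
| 2% | 1828 | 89.7% |
| 5% | 1786 | 89.0% |
| 10% | 1717 | 87.8% |

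**4. Bias at the carbocisteine margin, no true effect.** The hazard ratio here is for achieving unassisted breathing, so values above 1 favour the mucoactive. On this scale the planned effect is 1/0.86 = 1.16. Withdrawal is possible in all three mucoactive groups.

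Scenarios A and B use 489 per group, exponential times with median 7 days and 1500 runs. In A, each mucoactive patient has the same chance of withdrawing, whatever their ventilation time, and is censored before their own event. In B, the same average share withdraws, but only among patients ventilated for more than 7 days.

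| Share withdrawn | A: HR | A: type I error | B: HR | B: type I error |
|---|---|---|---|---|
| 2% | 0.994 | 4.9% | 1.003 | 4.9% |
| 5% | 0.988 | 6.1% | 1.012 | 6.2% |
| 10% | 0.974 | 8.8% | 1.022 | 7.8% |

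Scenario A is not independent censoring. A patient ventilated for longer has more time in which to withdraw, so an equal chance for everyone over-represents quick weaners among those censored. That is why its hazard ratio falls below 1. Withdrawal at a constant rate unrelated to prognosis would leave the hazard ratio at 1.00 and cost only events.

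Scenario C uses 464 per group and 3000 runs. It takes 30% of patients as slow (median 14 days) and the rest with median 5.5 days. Only slow mucoactive patients withdraw, at 0.01, 0.02 or 0.04 per day up to day 28. With h the withdrawal rate and k = ln 2/14 = 0.0495, the share withdrawn is 0.3 × h/(h + k) × (1 − exp(−28(h + k))), which is 4.1%, 7.4% and 12.3%.

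| Share withdrawn | HR | Type I error |
|---|---|---|
| 4.1% | 1.01 | 6.0% |
| 7.4% | 1.02 | 6.6% |
| 12.3% | 1.04 | 12.2% |

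In A and B, the same simulated patients analysed without censoring gave a hazard ratio of 1.00 throughout.

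**The case against.** **Event 6 may mean loss of data.** The missing-at-random wording suits patients whose data stop, and event 4 uses the same strategy only where follow-up fails. The authors may have meant this. But the article says withdrawal from the intervention, and its consent section separates that from withdrawal of data collection. If only loss of data was meant, the sentence still needs changing. Where data collection really is withdrawn, censoring under a stated assumption is reasonable.

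**The list sits under additional analyses, and the SAP may settle the matter.** The SAP is not at hand. However, the list is expressly for the primary outcome, assigns intention-to-treat to other events and is nowhere labelled a sensitivity analysis. The point concerns a rule that the article states, not one that it omits.

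**A hypothetical strategy is a legitimate choice, and strategies may differ between events.** This stands. The fault is using it for the primary outcome alongside an intention-to-treat statement that excludes it.

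Four stronger readings are tempting, and the documents do not support them.

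- *The censoring is wholly one-sided.* Run as 928 against 928 with withdrawal in one arm only, scenario C gives hazard ratios of 1.02, 1.04 and 1.07 and type I error of 7.5%, 12.6% and 29.8%. The main comparisons are factorial margins, whose non-use side also contains a mucoactive group.
- *The bias favours the mucoactive.* The direction depends on who withdraws, and the article gives no information on that.
- *Every stopping of the drug is censored.* The discontinuation criteria list drug-related serious adverse events and physician decisions on safety grounds separately from a patient's or representative's request to withdraw. The article does not say that the first two are censored.
- *Event 4 has the same fault.* It is already censored only where follow-up is not possible.

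**Conclusion.** The contradiction holds on the text. The primary analysis is defined as applying "regardless of the subsequent treatment they received", and event 6 then censors the same outcome when the intervention is withdrawn, without requiring that follow-up be lost. For patients who give up only the mucoactive, this discards an outcome that can be observed, and does so unequally across the groups: two against one at each factorial margin.

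The likely size is small to modest. Over the assumed range of about 2% to 12% of mucoactive patients withdrawn, the factorial-margin hazard ratio under no effect lies between about 0.97 and 1.04, against a planned effect of 1.16 on the same scale. Type I error lies between about 5% and 12%. At about 2% withdrawn the effect is negligible. At 10%, power falls from 90.1% to 87.8%. These figures rest on assumed withdrawal rates, assumed links between withdrawal and ventilation time, and exponential times or mixtures of them. They illustrate scale and do not predict the trial's result. The contradiction and its remedy do not depend on them.

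**What to change.** In the intercurrent-event paragraph of Methods for additional analyses, and in the SAP if it repeats the rule, divide event 6 in two.

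- **Only the mucoactive is withdrawn:** treatment-policy (intention-to-treat) strategy. Follow the patient to unassisted breathing, death or day 60 and analyse as randomised.
- **In-hospital data collection is also withdrawn:** censor at that point under the stated missing-at-random assumption.

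If the hypothetical version is of interest, keep it as a sensitivity analysis. The compliance sensitivity analysis already planned under Statistical methods is a natural place. Event 4 needs only its cross-reference to event 6 tidied.

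The cost is about one sentence. No new data are needed, because the withdrawn elements are already documented separately and the primary outcome is already collected. The clarification should be dated and made before the final analysis.
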